#### Sensitivity analysis of primary outcome

In order to corroborate the robustness of the primary outcome, the following sensitivity analyses will be performed:Per protocol analysis: estimation of the treatment effects in those participants who actually receive the intervention. For analytic purposes, these analyses will be restricted to participants who complied with the treatment protocol, defined as (i) completed all assessments required for the analysis, and (ii) received a minimal dose of the interventionIntention to treat multivariate regression analysis with imputation, and adjusting for the baseline variables used to impute missing data. For subjects with missing data at either time- point, scores will be imputed using multiple imputation with 20 resamples, and imputing baseline variables age, gender, diagnosis, number of episodes, depression symptoms, country of residence and any relevant data collected post-randomisation (specific analytic method will depend on patterns of missingness in the data). Missing data will be imputed using predictive mean matching, using the 10 nearest neighbours.As in (b) above, but using only observed data.

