
### Statistical analysis plan

Sample size was determined by power analysis using G*Power 3. Analyses were conducted on the primary endpoint (Brief QoL.BD score) at T1 relative to baseline. Based on our pilot study (intent-to-treat *d* = 0.52), and Brief QoL.BD change in comparable RCTs [22, 51], a between-group effect size of *d* = 0.4 was conservatively estimated. This small-to-moderate effect size is comparable to effect sizes found for adjunctive CBT on a range of outcomes in BD [78], and therefore can be considered a clinically important difference given the new intervention is low intensity, low cost, and high access. A sample size of 200 (100 in Mindfulness for Bipolar 2.0 and 100 in Psychoeducation for Bipolar) would provide at least 80% power (1-*β*) to detect an effect of this size at α = 0.05 (two-tailed). Attrition at immediate follow-up was conservatively estimated at 33% based on attrition rates in the pilot study and our earlier RCT of a web-based intervention for BD [39], so *N* = 300 randomised participants are required to generate the required sample size of 200 for the primary analysis.

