#### Secondary outcome measures

Treatment-related change in secondary outcomes analyses will be identical to those described above for the primary outcome. It is anticipated that relative to Psychoeducation, the Mindfulness condition will be associated with improvement in three outcomes: (a) self-rated state anxiety (DASS-Stress, DASS-Anxiety), (b) self-rated depression (QIDS-SR) and (c) clinician-rated depression (MADRS). It is also anticipated that relative to Psychoeducation, the Mindfulness condition will be associated with decreased dropout attrition.

Analysis of treatment-related change in remaining secondary outcomes will be exploratory. Time to first relapse will be analysed using multivariate survival analysis [79].

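### None of the three listed sensitivity analyses departs from missing at random, although 33% attrition is expected at T1 and some withdrawals may be related to outcome

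*Protocol article*

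**What the plan says.** The section *Sensitivity analysis of primary outcome* gives the list a purpose: "In order to corroborate the robustness of the primary outcome, the following sensitivity analyses will be performed". Three analyses follow.

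- **(a) Per protocol.** The set is "restricted to participants who complied with the treatment protocol, defined as (i) completed all assessments required for the analysis", plus a minimum exposure to the programme.
- **(b) Adjusted regression after multiple imputation**, with 20 imputations. The method is fixed: "Missing data will be imputed using predictive mean matching, using the 10 nearest neighbours". Six baseline variables are named as predictors, together with "any relevant data collected post-randomisation (specific analytic method will depend on patterns of missingness in the data").
- **(c) Observed cases.** "As in (b) above, but using only observed data".

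Three other places bear on the point.

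- The sample-size text in *Statistical analysis plan* says: "Attrition at immediate follow-up was conservatively estimated at 33% based on attrition rates in the pilot study".
- *Statistical analysis of primary outcome* promises to analyse everyone randomised and to pursue follow-up whatever the site usage. It excepts those who explicitly discontinue and those withdrawn on ethical grounds. *Risk management* says that withdrawal, decided case by case, might follow admission, mania or hypomania, psychosis or suicidal intent.
- *Secondary outcome measures*, under the analysis plan, predicts that "the Mindfulness condition will be associated with decreased dropout attrition".

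**The concern.** A sensitivity analysis for missing data is informative when it changes the assumption about the missing values. Here (a) and (c) leave non-responders out. In (b), each missing value is replaced by that of an observed participant with a similar predicted score. No entry lets non-responders do systematically worse, or better, than comparable responders.

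That matters because about a third of T1 scores may be missing, the outcome is self-reported, and one route out of follow-up is clinical deterioration, which plausibly goes with a lower unobserved quality-of-life score. If missingness depends on that score beyond what the model captures, the listed analyses can agree with each other on a biased estimate. Their agreement would then be reported as corroboration.

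**Working it through.** **1. The plan's own figures.** Inputs from *Statistical analysis plan*: d = 0.40, two-sided alpha 0.05, 100 evaluable per arm, 33% attrition, 300 randomised.

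- Power at 100 per arm is 0.804 (t-test) or 0.807 (normal approximation), so the stated 80% reproduces.
- 200 / (1 − 0.33) = 298.5, and 300 × 0.67 = 201, so the inflation to 300 reproduces. The sample size is not in question.

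**2. Smallest significant difference.** SE = √(2/100) = 0.1414. The threshold is t(0.975; 198) × SE = 1.972 × 0.1414 = 0.279.

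**3. Delta arithmetic.** Let p be the share missing and δ the shortfall of non-responders, in SD, relative to what MAR predicts (M = Mindfulness, P = Psychoeducation). Then

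effect = d(MAR) − p(M)·δ(M) + p(P)·δ(P).

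This is first-order: the SE is held at its observed-data value. Assume d(MAR) = 0.40.

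*Shortfall in Mindfulness only, p(M) = 0.33:*

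| δ(M), SD | Effect |
|---|---|
| 0.25 | 0.40 − 0.0825 = 0.318 |
| 0.50 | 0.40 − 0.165 = 0.235 |
| 1.00 | 0.40 − 0.33 = 0.070 |

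- Significance is lost at (0.40 − 0.279)/0.33 = 0.37 SD. The effect reaches zero at 0.40/0.33 = 1.21 SD.
- With p(M) = 0.28 assumed, significance is lost at (0.40 − 0.279)/0.28 = 0.43 SD.
- At the validation-sample SD of 8.76, 0.37 SD is 3.2 points. The article does not say which SD its d refers to, so this conversion is itself an assumption.

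*Same shortfall in both arms, with an assumed split of 28% (Mindfulness) and 38% (Psychoeducation):* effect = 0.40 + 0.10·δ, that is 0.425, 0.450 and 0.500 at δ = 0.25, 0.50 and 1.00. Here the MAR estimate is too small.

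**4. Can (b) and (c) disagree enough to warn?** Simulation with 150 per arm, 400 runs per scenario, an assumed baseline correlation of 0.6, and arm and baseline score in the model. Imputation was by predictive mean matching with 20 imputations and 10 donors.

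| Scenario | Missing, Mindfulness / Psychoeducation | True effect | Observed only | Imputed |
|---|---|---|---|---|
| MAR, dropout depends on arm and baseline | 29% / 38% | 0.40 | 0.404 | 0.393 |
| Outcome-dependent, Mindfulness only | 32% / 33% | 0 | 0.235 | 0.231 |
| Outcome-dependent, Mindfulness only | 32.5% / 33% | 0.40 | 0.646 | 0.636 |
| Outcome-dependent, same slope in both arms | 22% / 38% | 0.40 | 0.330 | 0.320 |

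In the last three rows both estimates are wrong by similar amounts and lie within about 0.01 of each other. The Mindfulness-only scenario is strong: a bias of 0.235 with 32.2% missing corresponds to a shortfall of about 0.235/0.322 = 0.73 SD. Analysis (a) was not simulated. It also conditions on completion, and adds selection on exposure after randomisation.

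**The case against.** Several counter-arguments have force.

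- **A reader might infer that robustness is never tested.** The document does not support that. The list varies adherence, the analysis set, covariate adjustment and imputed versus observed data. The gap is confined to departures from MAR.
- **A reader might infer that the predicted difference in dropout between arms already invalidates these analyses.** It does not. Dropout that depends on arm is compatible with MAR when arm is in the model, and the first simulated row shows essentially no bias. The article does not name arm among the imputation variables; the simulation assumes that it is included.
- **A reader might infer that the bias favours Mindfulness.** The plan predicts less dropout there. If non-responders do equally badly in both arms, the bias goes against Mindfulness.
- **The 0.37 SD figure is a one-arm worst case.** It gives Mindfulness the full 33% missing and Psychoeducation non-responders no shortfall. Most trials powered near 80% would lose significance under a similar penalty.
- **MAR may be more plausible than the bare list suggests.** Imputation may use data collected after randomisation. Telephone ratings and automatic usage records exist separately from the online questionnaire, and reminders, calls and vouchers support completion. Nothing shows that ethical withdrawals make up much of the 33%.
- **The article is condensed, and a full analysis plan may add such an analysis.** However, it gives an explicit list for a stated purpose, down to the number of donors. The clause leaving the method to depend on missingness patterns does not close the gap, because observed patterns cannot distinguish MAR from dependence on the unobserved score.

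These points limit the size and direction of the concern. They do not supply an analysis that departs from MAR.

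**Conclusion.** The point holds in a limited form. As listed, the sensitivity analyses cannot show whether the T1 conclusion survives outcome-related missingness, and agreement among them should not be presented as if it did. Follow-up exceptions that may coincide with clinical worsening are the better textual support; the attrition hypothesis alone is not enough.

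The figures of 0.37 SD (33% missing) and 0.43 SD (28% missing) illustrate sensitivity and do not predict bias. They rest on an assumed observed d of 0.40, 100 observed per arm (108 and 93 under the assumed 28%/38% split, with the same threshold to three decimals), a shortfall in Mindfulness alone and an unchanged SE. The simulated biases depend further on assumed dropout models. The sample size and the primary contrast are unaffected.

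**What to change.** Add to the list in *Sensitivity analysis of primary outcome* a delta-adjusted (tipping-point) multiple imputation analysis of the T1 contrast. Shift the imputed scores by deltas that vary separately in each arm over a range fixed before unblinding, and report the combinations at which the conclusion changes. Arm-specific deltas are needed because the direction of bias is uncertain.

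State also that the per-protocol analysis addresses adherence and is not evidence of robustness to missing data.

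The work reuses the planned imputations and needs no new data. It costs a little programming, one more table, and possibly a less favourable statement about robustness.

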### Trial design

The trial is a prospective, parallel group, rater-blind, superiority RCT with a one-to-one allocation ratio comparing the Mindfulness for Bipolar 2.0 intervention with a structurally equivalent, validated and therapeutically credible active control condition (Psychoeducation for Bipolar). The primary endpoint is immediately post-treatment (upon completion of the 5-week intervention). Follow-up time points are at 3-months and 6-months. Both interventions are guided self-help, and not intended to replace treatment as usual. The study setting is online, and participation in both arms occurs through a secure server.

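### Sensitivity analysis (b) fixes 20 imputations with one-third of T1 scores expected missing, so a borderline p-value there may not be reproducible; a minor point, fixed at almost no cost

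*Protocol article*

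**What the plan says.** Under *Sensitivity analysis of primary outcome*, the protocol article lists three analyses intended to support the primary result. The second, (b), is an intention-to-treat regression in which "scores will be imputed using multiple imputation with 20 resamples". The method is also fixed: "Missing data will be imputed using predictive mean matching, using the 10 nearest neighbours". The imputation model takes in several baseline variables and relevant post-randomisation data, and the exact technique is left open until the pattern of missing data is known. No decision rule is attached to (b).

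The sample-size paragraph under *Statistical analysis plan* gives the forecast: "Attrition at immediate follow-up was conservatively estimated at 33" per cent, so that 300 "randomised participants are required to generate the required sample size of 200 for the primary analysis". On the article's own figures, therefore, about one in three primary-outcome scores at T1 will be missing.

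**The concern.** Multiple imputation is itself a simulation, and a finite number of imputations adds noise that depends only on the random seed. That noise grows with the share of information that is missing and shrinks as imputations are added. Twenty is a small number for a variable that is one-third missing.

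At stake is the reproducibility of what (b) reports. Of the T1 analyses the article describes in detail, (b) is the only one that assigns a score to everyone randomised: the per-protocol analysis needs completed assessments, and (c) uses observed data only. If (b) lands near p = 0.05, two analysts who follow the plan on the same data could report different sides of the threshold and somewhat different confidence limits.

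**Working it through.** **Inputs from the article.** Imputations m = 20; 33% missing at T1; 300 randomised and 200 with data; 1:1 allocation; d = 0.4; two-sided α = 0.05; SD of the Brief QoL.BD 8.76 (*Primary outcome measure*).

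**Assumption.** The article gives no fraction of missing information (FMI). I take 0.33, with a range of 0.20 to 0.40. A simulation with N = 300, one-third missing and predictive mean matching on 10 neighbours gave 0.32 to 0.33.

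**The article's own figure.** With 100 per arm and d = 0.4, exact t-test power is 0.804, in line with "would provide at least 80% power". Inflation for attrition: 200 / 0.67 = 298.5, so 299 against the stated 300. Both figures reproduce.

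**Noise in the estimate.** Monte Carlo error / SE = √(FMI / m).

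| FMI | m = 20 | m = 100 | m needed for 5% (FMI / 0.05²) |
|---|---|---|---|
| 0.20 | 10.0% | 4.5% | 80 |
| 0.33 | 12.8% | 5.7% | 132 |
| 0.40 | 14.1% | 6.3% | 160 |

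In scale points, taking 100 observed per arm and no baseline adjustment: SE = 8.76 × √(2/100) = 1.24. The seed-to-seed SD of the estimate is 0.128 × 1.24 = 0.16 points.

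**Noise in the standard error.** Its coefficient of variation is about FMI / √(2(m − 1)) = 0.33 / √38 = 5.4%. A 95% confidence limit therefore has a seed-to-seed SD of about √(0.128² + (1.96 × 0.054)²) = 0.17 SE, or 0.2 points.

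**Effect on the p-value.** Call the p-value that unlimited imputations would give the long-run p. The results below come from simulating Rubin's rules with small-sample degrees of freedom at FMI 0.33.

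| Long-run p | 95% range at m = 20 | Seeds on the other side of 0.05, m = 20 | Same, m = 100 |
|---|---|---|---|
| 0.01 | 0.004–0.030 | 0.1% | 0% |
| 0.03 | 0.013–0.070 | 14% | 0.3% |
| 0.04 | 0.018–0.088 | 34% | 11.5% |
| 0.06 | 0.029–0.12 | 27% | 12% |
| 0.10 | 0.052–0.18 | 2% | 0% |

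A hand check of the p = 0.04 row: z = 2.05, with a seed-to-seed SD of about √(0.128² + (2.05 × 0.054)²) = 0.17. So z runs from about 1.72 to 2.38 and p from about 0.085 down to 0.017. Repeating that row at FMI 0.20 and 0.40 gives 25% and 38% of seeds above 0.05 at m = 20.

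**How often it matters.** Averaged over all trials at FMI 0.33, two seeds disagree on p < 0.05 as follows:

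- true d = 0.4: about 6% with m = 20, about 2% with m = 100;
- true d = 0.3: about 8% with m = 20, about 3% with m = 100;
- no true effect: about 2% with m = 20, about 1% with m = 100.

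Full simulations with predictive mean matching and a baseline score predictive of the outcome gave 1.6% to 6.6% at m = 20 and 0.8% to 3.4% at m = 100.

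**The case against.** The strongest reply is that nothing decisive hangs on (b). It is one of three supporting analyses and has no significance rule attached. Such analyses are usually read on the estimate and its interval, and these barely move: 0.16 points of seed noise against an SE of 1.24 and a reliable change of 3.16 points, about twenty times that noise. Relative efficiency at m = 20 is 1 / (1 + 0.33/20) = 0.984. This stands, and it sets the size of the point. It does not answer the narrower one, because efficiency describes average precision, not whether a reported p-value can be reproduced.

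Second, the noise depends on the imputation model. The article provides for baseline predictors and post-randomisation data, and calls its attrition figure conservative. If auxiliary data explained 25% to 50% of the residual variance and were fully observed, FMI would be about 0.27 to 0.20 and the Monte Carlo error about 12% to 10% of the SE. If people who drop out miss those measures too, little is gained. This also stands, and is why a range is given.

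Third, every finite m leaves some seed dependence, so 20 is imprecise rather than wrong. That is true, but moving to 100 cuts the disagreement by more than half for almost nothing.

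A reader might infer that the article is at fault for naming no seed and no Monte Carlo error limit. Those details may sit in a full analysis plan that is not shown, so their absence is not counted here.

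**Conclusion.** The point holds as a minor one. With 20 imputations and one-third of T1 scores missing, the simulation noise in (b) is about 13% of the standard error (10% to 14% over FMI 0.20 to 0.40). A long-run p between roughly 0.02 and 0.10 may then fall on either side of 0.05 depending on the seed. Outside that band the result is stable, and at the design effect two runs would agree in about 94% of trials.

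A reader might go further and infer that the trial's verdict can turn on the random seed. The article does not support that. Its section on the primary analysis gives no number of imputations, and it nowhere makes the primary conclusion depend on (b). The one-in-three figure applies only to a result already close to the threshold.

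The calculation rests on the assumed FMI and on 33% attrition being realised; less missing data would shrink the problem.

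**What to change.** Replace the 20 resamples in analysis (b) with at least 100 imputations, and raise the number until the Monte Carlo error of the treatment estimate is at most 5% of its standard error. At an FMI of 0.33, 100 imputations give 5.7%, so about 130 would be needed (0.33 / 0.05² = 132); at 0.20, 100 is already enough. Report the Monte Carlo error reached. The article says secondary outcomes will be analysed in the same way as the primary, so the same number should apply wherever imputation is used for them. With 300 participants the only cost is a little computing time, and the change does not touch the design, the data collected or the estimand.

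### Randomised arm is not among the listed imputation predictors, so sensitivity analysis (b), built as written, would pull the treatment effect toward zero

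*Protocol article*

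**What the plan says.** The section on sensitivity analysis of the primary outcome lists three analyses. Analysis (b) is an intention-to-treat regression after multiple imputation with 20 resamples, adjusted for the baseline variables used in the imputation. Scores missing at either time point are imputed. The predictors are given as "imputing baseline variables age, gender, diagnosis, number of episodes, depression symptoms, country of residence and any relevant data collected post-randomisation", and a parenthesis adds that the specific method will depend on the pattern of missing data. The technique is fixed: "Missing data will be imputed using predictive mean matching, using the 10 nearest neighbours". Analysis (c) repeats (b) on observed data only.

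The sample size paragraph of the statistical analysis plan section gives the planning figures: "a between-group effect size of *d* = 0.4 was conservatively estimated", and "Attrition at immediate follow-up was conservatively estimated at 33" per cent.

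The section on secondary outcome measures says that those outcomes are analysed in the same way as the primary outcome. It also expects lower dropout in the Mindfulness arm.

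**The concern.** An imputation model should contain every variable in the analysis model, above all the one whose effect is being estimated. Here that variable is randomised arm. Without it, a missing Mindfulness score and a missing Psychoeducation score with the same covariates are filled from the same donors in both arms. The imputed part of the data then carries little or no arm difference, and the pooled estimate is diluted by roughly the share that was imputed.

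Analysis (b) is meant to corroborate the primary result. If it is biased toward zero by construction, a real effect may look fragile. A gap between (b) and the observed-data analysis (c) could also be misread as a sign of informative dropout. Because the secondary outcomes borrow the same methods, the problem may carry over to DASS-21, QIDS-SR and MADRS. The protocol's own expectation of different dropout by arm is a further reason to have arm in the model.

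**Working it through.** **Inputs from the protocol.** d = 0.4; two-sided α = 0.05; at least 80% power; 100 evaluable per arm; 1:1 allocation; 33% attrition at T1; 300 randomised; 20 imputations; 10 nearest neighbours.

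**The plan's own figure.** n per arm = 2 × (1.96 + 0.842)² / 0.4² = 98.1, so 99. With 100 per arm, power is 80.7% (normal approximation) or 80.4% (noncentral t). Inflation: 200 / (1 − 0.33) = 299, or 200 / (1 − 1/3) = 300. The stated 200 and 300 are reproduced.

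**Expected dilution without arm.** Let the true T1 means be m1 and m0, with m1 − m0 = d, and let a share p be missing in each arm. If imputed values do not depend on arm, they average (m1 + m0)/2 in both arms. The completed-data difference is

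(1 − p) × m1 + p × (m1 + m0)/2 − [(1 − p) × m0 + p × (m1 + m0)/2] = (1 − p) × d.

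With p = 0.33 this is 0.67 × 0.4 = 0.27.

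Unequal dropout does not rescue the estimate. With completion shares c1 and c0 the retained fraction is 2·c1·c0 / (c1 + c0). For illustrative shares of 75% and 59% this is 2 × 0.75 × 0.59 / 1.34 = 0.66.

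**Simulation.** N = 300, one third of T1 missing completely at random and equally by arm, predictive mean matching with 10 neighbours, 20 imputations, Rubin's rules, 300 replicates. The analysis regression contained arm, baseline covariates and baseline QoL. Assumed, because the protocol does not give them: T0–T1 correlation 0.6, T1–T2 correlation 0.7, baseline depression–QoL correlation −0.6, and a T2 effect equal to the T1 effect. The Monte Carlo standard error is 0.004–0.007.

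| Imputation model | Mean estimate (true 0.40) | Shrinkage |
|---|---|---|
| Named baseline variables only | 0.256 | 36% |
| + baseline QoL.BD, no arm | 0.279 | 30% |
| + baseline QoL.BD, T2 score for 25% of those missing T1, no arm | 0.288 | 28% |
| same, T2 for 50% | 0.305 | 24% |
| same, T2 for 100% | 0.345 | 14% |
| No baseline QoL.BD, T2 for 50%, no arm | 0.303 | 24% |
| No baseline QoL.BD, T2 for 100%, no arm | 0.350 | 12–13% |
| Named baseline variables + arm | 0.400 | none |
| + baseline QoL.BD + arm | 0.397 | about 1% (within simulation error) |

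The first two rows lie on either side of the arithmetic value of 0.27, and the gap between them should not be read as an effect of baseline QoL.BD. A further simulation with 600 trials gave 0.27 in both cases.

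The share of simulated trials reaching significance was 61% with the named variables only and 88% with arm added to them. With T2 scores for everyone and no arm it was 92–95%. In that favourable case the damage is to the estimate rather than to the test.

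**The case against.** The strongest reply is that the list is not closed. It admits relevant post-randomisation data and leaves the specific method to the missingness pattern. It also doubles as the covariate list for the regression, where arm would not appear because arm is the effect being estimated. A journal article condenses a fuller plan, and imputation by arm would be compatible with the text. This stands in part: a reader might infer that the protocol excludes arm, but it is only silent. It does not follow that nothing needs changing. The text goes down to the number of donors and names six predictors, and arm, assigned at randomisation, is neither one of them nor naturally data collected afterwards. A programmer building the model from this text would leave it out.

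Four other inferences are tempting and not supported.

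- **That the loss is fixed at one third.** That is about the upper end. It needs 33% missing, which the protocol itself calls conservative, and no later QoL data.
- **That leaving out baseline Brief QoL.BD causes shrinkage.** It costs precision only; adding it without arm leaves the bias. Because T0 and T1 scores are both to be imputed, a chained model may carry it anyway.
- **That matching to donors from the other arm makes the bias worse.** This is the same mechanism described a second time.
- **That (b) is the only analysis able to use all 300 participants.** The mixed model for the QoL time trend, using T0 to T3, can also do so, because baseline questionnaires precede randomisation.

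It is also true that (b) is a sensitivity analysis, that the bias is toward no difference and so would not create a false positive, and that (c) gives a comparison on observed data.

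**Conclusion.** The point holds in this form: the predictors listed for analysis (b) omit randomised arm, imputation within arm is not stated, and following the list as written biases (b) toward zero. The size depends on what else enters the model: about a third at 33% missing with the named baseline variables alone, roughly 12–28% with later QoL scores for some or all of those missing T1, and none once arm is included. The one-third figure follows from the protocol's attrition by arithmetic. The 12–28% range rests on the assumed correlations, an effect sustained to T2, and missingness completely at random and equal by arm. If actual attrition is lower, the bias falls in proportion.

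The primary estimate and the sample size are not affected. The matter should still be settled before analysis, because a check meant to support the primary result should not be built to understate it, and the same method may be applied to the secondary outcomes.

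**What to change.** State in analysis (b) that missing scores are imputed separately within each randomised arm or, at the least, that arm is in the imputation model. Name baseline Brief QoL.BD and the T2 and T3 Brief QoL.BD scores as predictors. Including arm is what removes the bias; the QoL.BD scores add precision and make the missing-at-random assumption more plausible. Say that the same rule applies wherever the secondary outcomes are imputed.

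The cost is one sentence in the plan and a few lines of code. Imputing by arm shrinks the donor pool to about 150 × 0.67 ≈ 100 per arm, which is enough for 10 neighbours. If arm was always intended, the sentence only records it.
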